### Procedures

Recruitment in schools will include an informational email and video about the study, *RR*, coaching, and school-based teams. We will meet with school administrators via Zoom to share study information, participation requirements, and answer questions. We will then meet with educators to obtain consent and subsequently ask teachers to send recruitment materials (electronic/paper) to caregivers of focal students and classmates to participate in the Friendship Survey. The results of the Friendship Survey will determine social network inclusion status (isolated, peripheral, secondary, and nuclear). We will invite classmates who are classified as isolated, rejected, or peripheral and who may need additional support at recess (*n* = 1–2 per school) into the study.

An independent statistician will randomize all schools. The randomization (coaching with school-based teams vs. coaching only) has equal assignment probability to each group. Randomization will be stratified on the number of educators who will deliver *RR* (educators = 2 vs. > 2). Unmasking of randomization will not be permissible.

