### Participants

We will recruit 55 elementary schools across Washington, California, and Oregon. To be eligible, schools must have at least two educators directly involved with *RR* implementation, and at least two autistic students and/or students who are isolated, rejected, or peripheral on their classroom social network.

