#### Inclusion/exclusion

We will recruit *n* = 121 educators who attend recess and are school district employees, to ensure they have the capacity to participate in research activities. We also will recruit *n* = 55 general and/or special education teachers to complete study measures about students and school-level constructs and *n* = 83–138 other school personnel (e.g., administrators, teachers) to serve on the school-based teams (approximately 3–5 participants). Participants will remain in the study for 18 months unless they withdraw or change jobs. School personnel involved with *RR* coaching will receive $50 for their data completion. School personnel involved with school-based teams will receive $25 per session and $25 for their data completion. Teachers will receive $25 for their data completion and an additional $10 per student per data collection timepoint.

We will recruit 118 autistic students and allistic classmates. Autistic students will be included if they: 1) have a documented autism classification; 2) are between the ages of 5–12 and enrolled in Kindergarten through 5th grade; and 3) share a recess period with allistic peers. Allistic classmates will be included if they are: 1) isolated or peripheral on their classroom social network; and 2) require support during recess. Autistic students and their peers without an available educator supporting recess will be excluded. Participants will not be excluded given their sex, gender identity, age, or racial/ethnic background, and will not be asked to disrupt any other service utilization.

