### Data analysis

All subjects, once randomized, will be included in the intent-to-treat sample, and every effort will be made to collect all primary and secondary outcomes even if the participant (educator, school personnel, or student) does not engage in randomly assigned treatments.

#### Primary aim 1

Primary Aim 1 analysis will contrast coaching with school-based teams vs. coaching only on change in *RR* fidelity (primary outcome) and students’ peer engagement (secondary outcome) from T1-T5. Generalized linear mixed models (GLMM) will be used to analyze change in T1-T5 for *RR* fidelity and sustainment as well as peer engagement and from T1-T3 for all other social outcomes. Separate models will be fitted for each primary and secondary outcome and a piecewise-linear model with potential knot(s) at T2 and T3, will be used to model the temporal trajectories across the study as the trajectories of the outcomes may occur at the end of each semester. The analysis will fit a GLMM with fixed effects for the intercept, time, and a group-by-time interaction. The GLMM will include random effects for the intercept and time (slope) and model the correlation between the two random effects. All outcomes will be assessed for normality. If outcomes are non-normally distributed, other distributions will be assumed or transformations of the outcomes will be considered. The GLMM also can be extended to model the nesting effects (e.g., educators nested within schools or students nested within classrooms or educators). The GLMM will adjust for the following baseline measures X when evaluating the primary outcome—*RR* fidelity: site and years of experience at current position. For models evaluating student outcomes, the GLMM will adjust for X: site and child’s age. The primary aim contrast in this study is the between groups difference in change in outcomes from T1-T5 for *RR* fidelity and sustainment as well as playground engagement and between group differences in changes from T1-T3 for all other student outcomes.

#### Secondary aim 2

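### School randomisation is stratified only on educator number, which on the stated targets separates at most 11 of 55 schools, while site, a covariate in the fidelity and student-outcome models, is left to chance

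*Protocol article*

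**What the plan says.** All places are in the protocol article.

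- **Procedures.** An independent statistician randomises schools, and the randomisation "has equal assignment probability to each group". The only stratification factor is given as "Randomization will be stratified on the number of educators who will deliver" the intervention, in two levels: "educators = 2 vs. > 2".
- **Participants.** "We will recruit 55 elementary schools across Washington, California, and Oregon". To be eligible, "schools must have at least two educators directly involved with" delivery.
- **Inclusion/exclusion.** The recruitment target is "121 educators who attend recess and are school district employees".
- **Data analysis, Primary aim 1.** The fidelity model adjusts for "site and years of experience at current position". The student-outcome models adjust for site and the child's age. The stated fixed effects are an intercept, time and group by time. The primary contrast is the difference between groups in change over time. No site-by-time term is mentioned.
- **Cost Analysis.** Personnel time is priced from national or state sources, geographic price variation is characterised where needed, and sensitivity analyses are planned. No site adjustment of the arm comparison is stated.

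The abstract calls the study multi-site. The article gives neither the number of research sites nor the number of schools at each.

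**The concern.** Only 55 units are randomised, so the choice of stratification factors matters more than in a large trial of individuals. The single factor chosen splits the schools very unevenly on the plan's own targets. Site is known for every school before allocation, and the plan treats it as prognostic by adjusting for it in the fidelity and student-outcome models, yet it plays no part in the allocation.

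Three things are at stake:

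1. **Precision.** The site-adjusted contrast loses information when arms are unequal within sites.
2. **Chance error in the group-by-time estimate.** The primary contrast concerns change. A site main effect removes differences in level between sites. It does not remove differences in slope that fall unevenly across arms by chance.
3. **Unadjusted comparisons.** Raw arm summaries and the arm cost comparison have no stated site adjustment, so a chance imbalance in site remains in them.

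**Working it through.** **Inputs from the documents.** 55 schools; at least 2 educators per school (Participants); 121 educators (Inclusion/exclusion); equal allocation with one two-level stratification factor (Procedures); 98 educators before inflation, 10% attrition and 10% clustering inflation, target slope difference 0.15, 80% power (Sample size and power considerations).

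**Step 1: the plan's own figure.** 98 / 0.9 / 0.9 = 120.99, which rounds up to 121. The stated total is reproduced.

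**Step 2: size of the upper stratum.** Schools with more than two educators <= 121 - 2 x 55 = 11, and 11/55 = 20%. At least 44 schools (80%) share the other stratum. The mean is 121/55 = 2.2 educators per school. If all 11 schools had exactly three educators, they would hold 33 of 121 educators (27%).

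**Step 3: site balance under the present scheme.** Site numbers and sizes are assumptions, because the article gives none. Schools were allocated 1:1 within the two educator strata (11 and 44 schools) and compared with permuted blocks of 4 within site. For site s with n1 and n0 schools in the two arms and n in total, the information on the site-adjusted arm contrast is the sum over sites of n1 x n0 / n, relative to 55/4 = 13.75 at perfect balance.

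| Assumed sites | P(gap >= 4 schools in some site) | P(gap >= 6) | Mean information loss | Loss exceeded in worst 5% |
|---|---|---|---|---|
| 28/27 | 0.43 | 0.18 | 1.9% | 7.5% |
| 19/18/18 | 0.63 | 0.30 | 3.8% | 11.0% |
| 27/18/10 | 0.59 | 0.25 | 3.7% | 10.3% |
| 35/10/10 | 0.54 | 0.19 | 3.7% | 9.9% |

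With blocks within site, the chance of a gap of four or more was 0 in every layout and the mean loss was at most 0.5%. If there were four sites (14/14/14/13), the present scheme would give a mean loss of 5.6%, with 14% exceeded in the worst 5%.

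One allocation by hand, with splits 12:6, 8:10 and 8:11: 72/18 + 80/18 + 88/19 = 4.00 + 4.44 + 4.63 = 13.08. Then 13.08/13.75 = 0.951, a loss of 4.9%.

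**Step 4: what this means for power.** Starting from 80% power, 1.96 + 0.84 = 2.80 standard errors. With a 4% loss, 2.80 x sqrt(0.96) = 2.745 and power is about 78%. With an 11% loss, 2.80 x sqrt(0.89) = 2.64 and power is about 75%.

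**Step 5: site trajectories.** Take the same splits (28:27 overall) and assume that the first site's slope is higher by 0.15, the plan's own detectable difference. That site supplies 12/28 = 0.429 of one arm and 6/27 = 0.222 of the other. With no allowance for site, the spurious slope difference would be 0.15 x (0.429 - 0.222) = 0.031. A generalised least squares calculation with three equally spaced time points, a random intercept and slope, and several assumed sets of variances, with site as a main effect only, leaves 0.02 to 0.03. That is about 14% to 20% of 0.15. With a site-by-time term it is zero. The site slope difference is an assumption chosen for illustration; the result scales in proportion to it.

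**The case against.** The strongest reply is that the plan already deals with site by adjusting for it in the fidelity and student-outcome models. Chance imbalance under a valid randomisation is not bias, and the usual cost is a few percent of information. That stands, and it sets the size of the point. It does not fully cover the primary contrast, because the model as described adjusts for site level only. A fuller analysis plan may add a site-by-time term; the article does not mention one.

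Second, stratifying on educator number has a purpose: it balances cluster size when schools are randomised and educators are analysed. The upper stratum could hold 27% of educators. A reader might infer that the present stratification achieves next to nothing. The documents do not support that, and the limit of 11 schools belongs to the recruitment target, so it would rise if more than 121 educators enrolled.

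Third, a reader might infer that coaches differ between sites, so that coaching delivery is mixed up with arm. No section ties coaches, facilitators or observers to a site. Data collection has experts coaching over Zoom, and Coaching describes an approach intended to keep training consistent across sites. What supports site as a factor is that the models adjust for it and that schools are drawn from three states.

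Fourth, the cost section does not ignore geography. It allows for describing price variation where needed and plans sensitivity analyses, but that is not an adjustment of the arm comparison for site.

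**Conclusion.** The point holds as an avoidable weakness of design. On the stated targets, the only stratification factor separates at most 11 of 55 schools, and the balance of a covariate that the plan itself adjusts for is left to chance.

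It would be wrong to read this as confounding of site with arm. The randomised contrast is unbiased over allocations, and the planned adjustment removes differences in site level. What remains is a mean information loss of about 2% to 4%, with about 7% to 11% exceeded in the worst 5% of allocations; some chance error in the group-by-time estimate if sites change at different rates; and unadjusted cost and raw summaries.

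The limit of 11 schools follows directly from the documents. The probabilities and losses rest on assumed layouts of two or three sites and would be larger with more sites. The trajectory figure also rests on an assumed slope difference and assumed variances.

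**What to change.** In Procedures, add research site as a stratification factor, with permuted blocks within site, and state the number of sites. Keep educator number (2 versus more than 2) as a second balancing factor. Full crossing may leave sparse cells: 11 schools spread evenly over three sites would be 11/3, or between 3 and 4, in each upper cell, and the spread need not be even. If so, use minimisation or covariate-constrained allocation for the second factor. Keep site in the outcome models.

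The cost is a change to the randomisation paragraph, a new allocation list from the independent statistician, and slightly looser balance on educator number. The Discussion reports no enrolment as of September 2024. The change can apply only to schools not yet randomised.

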#### Data collection

Data will be collected during the following timepoints: T1 = baseline; T2 = Exit of *RR* 1; T = 3 End of Year 1; T4 = fall, the following school year; and T5 = spring, the following school year***.*** At baseline, we will collect demographics from all participants, as well as time in inclusion from teachers and autism symptomatology from caregivers. We also will ask caregivers to rate the quality of play for their child at all timepoints (T1-T5). A masked rater will code *RR* fidelity and peer engagement at all timepoints (T1-T5) provided the student remains at the school the following year. Educators and school-based teams members will be asked to complete acceptability and a cost survey at T1-T5 and rate sustainment at T4-T5. All consented students will be administered the Friendship Survey (~ 5–10 min) at T1-T3, and teachers will be asked to complete a measure of social skills per enrolled student at T1-T3. We will continue to collect implementation outcomes the following school year. Educators, teachers, and school-based team members will be asked to rate implementation leadership and climate and team processes at T1-T5. Participants will be assigned a numerical code. De-identified data will be entered into REDCap, and all efforts will be made to prevent risks. Progress reports will be submitted as required. De-identified data will be shared with the National Database for Autism Research twice a year.

Schools will receive an initial 60–90-min didactic at the start of the school year, followed by 20–30 min of weekly coaching. *RR* experts will provide both the initial training and weekly coaching via Zoom. Research staff will receive training to reliably administer measures and achieve coaching and school-based teams fidelity.

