#### Sample size and power considerations

The sample size for the study (*n* = 121 educators, *n* = 118 students in *n* = 55 elementary schools) was determined based on statistical power for the Primary Aim 1 contrast, a between implementation strategies (coaching with school-based teams vs. coaching only) mean comparison in change in *RR* fidelity (primary outcome) from T1-T3. Based on a Type-I error rate of 5%, a within-person correlation in paraeducator fidelity of ICC = 0.36 (based on preliminary data), a total number of 98 educators are needed to detect a difference of at least 0.15 in the comparison of slopes in educator’s *RR* fidelity with 80% power. After accounting for an estimated attrition rate of 10% and a 10% variance inflation factor for clustering by school, a total number of *N* = 121 is needed. Similarly, for our Primary Aim 1 secondary outcome, peer engagement, assuming a Type-I error rate of 5%, a within-person correlation in students’ joint engagement of ICC = 0.18 (based on preliminary data), a total number of 118 students are needed to detect a difference of at least 14% in total time spent in joint engagement in the comparison of slopes in joint engagement between coaching with school-based teams vs. coaching only with 80% power and 10% attrition and 10% variance inflation factor for clustering by school.

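### Year-two coding of educator fidelity is tied to the student staying at the school, and the 10% attrition allowance is not justified for the T1-T5 contrasts

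*Protocol article*

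**What the plan says.** Under Data collection, T4 and T5 are placed in the autumn and spring of the following school year. The masked rater codes RR fidelity and peer engagement "at all timepoints (T1-T5) provided the student remains at the school the following year": one verb, two outcomes, one proviso. The same section later says, with no such condition, that implementation outcomes go on being collected the next year. Tables 2 and 4 list fidelity at T1-T5, also without a condition. Under Implementation outcomes, fidelity is scored on what the educator does at recess: components used, and the quality of their delivery.

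Under Inclusion/exclusion, autistic students qualify if they "are between the ages of 5–12 and enrolled in Kindergarten through 5th grade". No criterion asks that the student can still be at the school the next year.

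Under Data analysis, Primary aim 1, the contrast runs over T1-T5 for fidelity, sustainment and playground engagement.

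Under Sample size and power considerations, the powered quantity is change in "fidelity (primary outcome) from T1-T3". The inflation for educators is made "with 80% power. After accounting for an estimated attrition rate of 10% and a 10% variance inflation factor for clustering by school". The student calculation is made "with 80% power and 10% attrition and 10% variance inflation factor for clustering by school" and names no time window. No separate attrition figure for the second school year appears.

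**The concern.** Two things do not fit together.

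First, the unit of the condition is wrong for fidelity. An educator who is still employed and still working recess can be observed whether or not a particular child has moved on. Followed literally, the rule leaves that educator without T4-T5 data on the primary outcome for a reason that has nothing to do with the educator.

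Second, the design contains a foreseeable exit between T3 and T4, analyses across it, and makes no allowance for it. Where a school's last grade is 5th, a 5th grader enrolled in year one is gone by T4. The 10% was set for a within-year comparison (fidelity) or for an unspecified one (students), so the stated 80% power cannot simply be read across to the T1-T5 contrasts. Year-two observations that are not made cannot be recovered later.

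**Working it through.** **Inputs.** From Sample size and power considerations: 80% power; 5% type I error (two-sided assumed, since sidedness is not given); 10% attrition; 10% clustering allowance; "a total number of 98 educators are needed to detect a difference of at least 0.15 in the comparison of slopes"; "a within-person correlation in paraeducator fidelity of ICC = 0.36"; 0.18 as the corresponding correlation for joint engagement; 118 students. Assumed, because the document gives neither: schools end at 5th grade, and students are spread evenly over the six grades from Kindergarten to 5th.

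**1. The plan's own figure.** 98 / (0.9 × 0.9) = 120.99, so 121 educators is reproduced. The bases (98 educators, and about 118 × 0.81 = 95.6 students) cannot be re-derived because no standard deviation is given. Power below is therefore scaled from the plan's own 80%: power = Φ(2.80 × √r − 1.96), where 2.80 = 1.96 + 0.84 and r is information relative to plan.

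**2. Structural loss of students.**
- Planned to remain: 118 × 0.9 = 106.2.
- After 5th-grade exit: 118 × 5/6 = 98.3, a loss of 16.7%.
- With the planned 10% added: 98.3 × 0.9 = 88.5, a total loss of 25%.
- With 5% other loss instead: 1 − (5/6 × 0.95) = 20.8%.

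**3. Power on complete cases.** r = 88.5 / 106.2 = 0.833, so power = Φ(2.80 × 0.913 − 1.96) = Φ(0.60) = 72.5%. By 5th-grade share, with 10% other loss throughout:

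| 5th-grade share | Students left at T4-T5 | Total loss | Power |
|---|---|---|---|
| 5% | 100.9 | 14.5% | 78% |
| 10% | 95.6 | 19% | 76% |
| 16.7% | 88.5 | 25% | 72% |
| 25% | 79.7 | 32.5% | 68% |

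**4. Power in the planned mixed model.** Leavers still contribute T1-T3. Take five equally spaced visits and correlation matrix V = (1 − ρ)I + ρJ. The information per student on intercept and slope is X′V⁻¹X. With a fraction q seen at T1-T3 only, the pooled information is (1 − q) × (five-visit information) + q × (three-visit information). Efficiency for the slope, relative to no loss:

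| Total loss q | Peer engagement (ρ = 0.18) | Fidelity (ρ = 0.36) |
|---|---|---|
| 10% (plan) | 0.937 | 0.930 |
| 20.8% | 0.865 | 0.852 |
| 25% | 0.836 | 0.822 |

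Relative to plan at 25% loss: 0.836 / 0.937 = 0.892 gives 75.4% power for peer engagement, and 0.822 / 0.930 = 0.884 gives 75.0% for fidelity. At 20.8% loss: 0.865 / 0.937 = 0.923 gives 76.8%, and 0.852 / 0.930 = 0.916 gives 76.5%. So roughly 75-77%. Using the simple T5 minus T1 difference instead changes these by less than half a point.

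**5. Fidelity, if the condition is applied.** There is about one student per educator (118 / 121 = 0.98). If each educator depends on one student, the losses in step 2 carry over. If either of two linked students is enough, the structural loss is (1/6)² = 2.8%, or 1 − 0.972 × 0.9 = 12.5% with the planned 10%. The document does not say which applies.

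**6. When 10% would suffice.** Total loss stays at or below 10% if the 5th-grade share is at most 10% with no other loss, or about 5% with 5% other loss (1 − 0.95 × 0.95 = 9.75%).

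**The case against.** The sentence under Data collection can be read as attaching the condition to peer engagement alone. The unconditional statement about implementation outcomes, the two tables, and the commitment under Data analysis to make every effort to collect all outcomes all favour that reading. This stands as an argument about intent. It does not clear the wording: the grammar covers both outcomes, and observers in the field would work from it.

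The documents give neither the grade mix nor the last grade of the schools, and the K-5 limit is written for autistic students only. This stands. A reader might infer that 10% attrition is impossible; step 6 shows it is not. What the text supports is that 10% is not justified for T1-T5.

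The 72% treats leavers as wholly lost, whereas the planned likelihood-based model keeps their first-year data. This also stands, and it is why 75-77% is the fairer figure for the planned analysis. More generally, with no standard deviation and no window for students, absolute power for T1-T5 cannot be derived from this article; the figures show the fall from a nominal 80%.

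A reader might also infer bias between arms. Ageing out is fixed by baseline grade and does not depend on allocation, and the student models adjust for age, so the documents do not support that.

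Finally, RR is individualised to students, so coding fidelity without the original child is a measurement decision as well as an edit. That is fair and belongs among the costs.

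**Conclusion.** The point holds in a limited form. As worded, the rule ties T4-T5 coding of an educator-level primary outcome to a student's continued presence, in conflict with the unconditional T1-T5 schedule elsewhere in the article. Separately, the 10% attrition allowance has no stated basis for the T1-T5 contrasts.

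Under an even grade mix in schools ending at 5th grade, and with the plan's own 10% added, year-two student loss is about 25%. That costs about 8 points of power on complete cases and about 3 to 5 points in the mixed model. The mixed-model figures assume compound symmetry, equal spacing and leavers missing both T4 and T5; the planned piecewise model with random slopes would shift them somewhat. The effect shrinks if few 5th graders enrol or schools run past 5th grade.

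The consequence is reduced precision and avoidable loss of primary-outcome data. It is worth correcting, because the Discussion reports no enrolment as of September 2024 and most of the remedy is wording.

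**What to change.** - **Data collection.** Reword so that fidelity is coded at T4 and T5 for every enrolled educator still working recess at the school, whether or not the focal student remains. Keep the student condition for the playground observation of peer engagement only.
- **Peer engagement contrast.** Either make T1-T3 the powered contrast, with T4-T5 secondary, or keep T1-T5 and restate attrition and power with a year-two allowance. In the second case, state the expected 5th-grade share, the last grade of participating schools and the other loss assumed.
- **Fidelity power.** Give the window to which the 10% applies, and add a year-two allowance if T1-T5 remains the contrast.

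Cost: the stated T1-T5 power becomes less favourable. Holding 80% on complete cases at 25% loss would need 106.2 / 0.75 = 141.6, so 142 students. If the student condition stayed on fidelity with one student per educator, it would need 98 / (0.9 × 0.75) = 145.2, so 146 educators. Some fidelity observations would take place without the original focal student, so the coding instructions should say how those are scored. The article gives no budget, so the cost of any extra observations cannot be judged from it.

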## Method

A hybrid type 3 effectiveness-implementation trial will be conducted (Fig. 2). After baseline assessments at the beginning of the school year, all schools will be provided *RR* training (Table 2). Schools will be randomized to coaching with school-based teams or coaching only.

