#### Organizational mediators

*Implementation Leadership.*Educators will complete the School Implementation Leadership Scale (S-ILS) [72], a 21-item measure that assesses seven subscales of implementation leadership: knowledgeable (understanding of *RR* and implementation issues), supportive (support for *RR* use), proactive (anticipating and addressing challenges), perseverant (consistent and responsive to challenges), communicative (shares implementation related information with staff), has a vision/mission (oriented towards using *RR*), and available in implementing *RR* [39, 75]. The S-ILS is a psychometrically validated and reliable instrument (α = 0.95–0.98). Implementation leadership is scored using aggregate individual ratings to the school level.

*Implementation Climate*. Participating educators will complete the School Implementation Climate Scale (S-ICS) [76], a 21-item measure that assesses seven subscales of implementation climate: focus, educational support, recognition, rewards, use of data, existing supports, and *RR *integration [75, 76]. The S-ICS is a psychometrically validated and reliable instrument (α = 0.81–0.91; 39, 79). Implementation climate is scored using aggregate individual ratings to the school.

*Team Processes.* TEAM members will complete the Team Processes Survey (TPS) [77] short form, a 10-item self-report of team processes (mission analysis, goal specification, strategy formulation and planning, monitoring progress toward goals, systems monitoring, team monitoring and backup, coordination, conflict management, motivation, and confidence building, and affect management). Responses are structured on a 5-point Likert-type scale from “1” = not at all to “5” = to a very great extent. The TPS has good internal consistency (α = 0.82–0.85). Table 4 outlines the complete study timeline, including data collection timepoints.

**Table 4 Tab4:** SPIRIT Flow Diagram

Activity	Study Period				
	**T1**	**T2**	**T3**	**T4**	**T5**
Enrollment					
Eligibility screen	X				
Informed consent	X				
Randomization	X				
Interventions					
Coaching	X	X			
TEAM	X	X			
Measures					
Demographics	X				
Autism classification	X				
Fidelity	X	X	X	X	X
Sustainment				X	X
Acceptability	X	X	X	X	X
Cost	X	X	X	X	X
Peer Engagement	X	X	X	X	X
Social Network Inclusion	X	X	X		
Social Skills	X	X	X		
Implementation Leadership	X	X	X	X	X
Implementation Climate	X	X	X	X	X
Team Processes	X	X	X	X	X

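### The article conflicts on who rates leadership and climate; if team members' ratings count, rater role is confounded with arm for these mediators and for PRESS sustainment

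*Protocol article*

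**What the plan says.** Three places in the protocol article say who rates the school-level mediators.

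- **Data collection:** "Educators, teachers, and school-based team members will be asked to rate implementation leadership and climate and team processes at T1-T5".
- **Table 2:** paraeducators, teachers and TEAM are the data sources for both the S-ILS (leadership) and the S-ICS (climate).
- **Organizational mediators:** educators alone are named as completing the S-ILS and S-ICS. On scoring it says: "Implementation leadership is scored using aggregate individual ratings to the school level". Climate has a parallel sentence.

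For sustainment, Data collection says: "Educators and school-based teams members will be asked to complete acceptability and a cost survey at T1-T5 and rate sustainment at T4-T5". Table 2 gives paraeducators and TEAM as the PRESS sources, with a raw score. The Sustainment paragraph sets the PRESS at T4 and T5 and gives no rule for combining raters.

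On the arms: "Schools will be randomized to coaching with school-based teams or coaching only". Inclusion/exclusion describes the team members as "83–138 other school personnel (e.g., administrators, teachers) to serve on the school-based teams (approximately 3–5 participants"), listed separately from the 121 educators and 55 teachers. No corresponding staff are named as raters in coaching-only schools.

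**The concern.** A school score built from all listed raters would have a different composition in each arm, and allocation itself would cause that difference. Randomization balances schools and staff. It does not balance a rater group that is created in only one arm.

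Equal rating across roles cannot be taken for granted. Table 3 places administrators on the teams, so some members may be rating leadership that they themselves provide, and all members take part in the strategy under test.

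Leadership and climate are the two proposed mediators, so the path from arm to mediator in Secondary Aim 2 is exposed. Sustainment is part of the Primary Aim 1 hypothesis and is one of the effectiveness measures for the cost-effectiveness ratios.

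**Working it through.** **Step 1. Are team members in one arm only?** Inputs: 55 schools (Participants), equal allocation (Procedures), teams of about 3–5, and a total of 83–138 (Inclusion/exclusion).

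- Schools per arm: 55 / 2 = 27.5.
- Teams in half the schools: 27.5 × 3 = 82.5, rounded up to 83; 27.5 × 5 = 137.5, rounded up to 138. The plan's own range is reproduced exactly.
- Teams in all schools would need 55 × 3 = 165 to 55 × 5 = 275.

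The stated headcount therefore means one arm.

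**Step 2. Share of ratings from team members, if every listed rater counts.** Educators per school: 121 / 55 = 2.2. Teachers per school: 55 / 55 = 1. Share = team members / (team members + raters present in both arms).

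| Measure | Raters in both arms | Team of 3 | Team of 5 | Coaching only |
|---|---|---|---|---|
| S-ILS, S-ICS | 3.2 | 3 / 6.2 = 48% | 5 / 8.2 = 61% | 0% |
| PRESS | 2.2 | 3 / 5.2 = 58% | 5 / 7.2 = 69% | 0% |

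These are upper values because they assume that no team member is also a study educator or teacher. If one member of a team of three were the study teacher, the leadership and climate share would be 2 / 5.2 = 38%. If one were a study educator, the PRESS share would be 2 / 4.2 = 48%.

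**Step 3. Offset at a single timepoint with no true strategy effect.** Offset = share × difference between team members and other raters in the same school. The article gives no such difference. Assumed: 0.2–0.5 of a rater-level SD, in either direction.

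- Leadership and climate: 0.484 × 0.2 = 0.10 SD to 0.610 × 0.5 = 0.30 SD.
- PRESS: 0.577 × 0.2 = 0.12 SD to 0.694 × 0.5 = 0.35 SD.

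**Step 4. Does the planned change contrast remove it?** Primary Aim 1 contrasts change between arms, and Secondary Aim 2 extends those models.

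- If the same team members also rate at T1 and the offset is constant, it cancels in a model with a group main effect.
- The fixed effects listed under Primary aim 1 are an intercept, time and the interaction of group with time, with no group main effect. Generalized least squares with those three terms, times 0, 1 and 2 for T1–T3, and an assumed constant within-unit correlation of 0.36 or 0.6 gives an interaction slope of 0.358 or 0.214 per unit of offset. Over two intervals, 72% or 43% of the offset enters the T1–T3 contrast. With a group main effect it is 0%.
- If team members start rating only after T1, the offset does not cancel.
- The PRESS has no T1–T3 measurement, so no baseline exists to subtract. A constant offset would cancel in a T4-to-T5 change but not in a comparison of levels.

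**The case against.** The strongest reply is that pooling across roles is not settled by the text. Data collection and Table 2 list who is asked to rate. The only scoring statements stand in the section on organizational mediators, and read alone that section aggregates educators' ratings, which both arms have. On that reading the mediator problem disappears. This stands, and it is why the point is conditional. But two of the three places name team members as raters, so the conflict decides whether the mediators are comparable between arms.

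For the PRESS, pooling is inferred from the list of sources and the raw score; the article does not state it. Primary aim 1 allows nesting of educators within schools, so individual scores may be modelled. That does not remove the concern: without restriction to common roles or a term for rater role, team members' ratings still enter one arm only.

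Choice of raters is often left to an analysis plan. Here, however, the article makes conflicting statements about it.

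A reader might also infer more than the documents support:

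- **That the results are biased toward the team arm.** The direction is unknown. Teams are convened to identify barriers, which could lower their ratings.
- **That team members cannot rate at T1 before allocation.** The article does not say when they are recruited, and facilitators are to build on existing teams, so candidates could be identified early.
- **That acceptability is affected in the same way.** It has the same raters as the PRESS, but no stated arm contrast uses it.

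**Conclusion.** The point holds in conditional form. The article contradicts itself on who rates leadership and climate. If Data collection and Table 2 are followed and all raters are used, rater role is confounded with arm for both mediators and for PRESS sustainment.

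The headcount result is firm. The shares assume no overlap between team members and study educators or teachers. The offsets rest wholly on the assumed 0.2–0.5 SD and apply to a single timepoint, so they show scale and do not estimate bias in the planned change contrast. Sustainment is the more exposed measure, because it has no baseline and because correcting the S-ILS and S-ICS rater lists would not resolve it.

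The arm contrast on the primary outcome is untouched: a masked observer codes fidelity. Only the mediation analysis of fidelity is exposed.

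**What to change.** 1. Reconcile Data collection, Organizational mediators and Table 2 so that each names the same raters for the S-ILS and S-ICS.
2. For between-arm contrasts and mediation, score the S-ILS and S-ICS from educators and teachers (or educators only) and the PRESS from educators only. These roles exist in both arms.
3. Report team-member ratings separately, within the team arm.

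Under this rule the raters per school are about 3.2 for the mediators and 2.2 for the PRESS in both arms, so the rater-mix offset is zero. The trial sample size does not change. The cost is precision: in the team arm the mediator scores rest on about 3.2 raters instead of 6.2–8.2, and the PRESS on 2.2 instead of 5.2–7.2, so scores there are somewhat noisier. The article reports no enrollment as of September 2024, and this is a scoring rule that needs no new data collection.
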